## Abstract

**Background:**

Early integration of palliative care concurrently to standard cancer care is associated with several benefits for patients and their caregivers. However, communication barriers on part of the caring physicians often impede a timely referral to palliative care. This study describes the protocol of the evaluation of a communication skills training aiming to strengthen the ability of physicians to address palliative care related topics adequately and early during disease trajectory.

**Methods:**

We will implement a communication skills training and evaluate it within a prospective, multi-centered, two-armed randomized controlled trial (RCT), which will be conducted at four sites in Germany. Eligible subjects are all physicians treating patients with advanced cancer in their daily routine. An intervention group (IG) receiving a group training will be compared to a wait-list control group (CG) receiving the training after completion of data collection. At pre- and post-measurement points, participants will conduct videotaped conversations with standardized simulated patients (SP). Primary outcome will be the external rating of communication skills and consulting competencies addressing palliative care related topics. Secondary outcomes on core concepts of palliative care, basic knowledge, attitudes, confidence and self-efficacy will be assessed by standardized questionnaires and self-developed items. A further external assessment of the quality of physician-patient-interaction will be conducted by the SP. Longitudinal quantitative data will be analyzed using covariate-adjusted linear mixed-models.

**Discussion:**

If the communication skills training proves to be effective, it will provide a feasible intervention to promote an earlier communication of palliative care related topics in the care of advanced cancer patients. This would help to further establish early integration of palliative care as it is recommended by national and international guidelines.

**Trial registration:**

German Clinical Trials Register DRKS00017025 (date of registration: 4 June 2019).

## Background

Complex psychological and physical symptoms of patients with advanced cancer often arise early during disease trajectory [1]. That is why palliative care, which focusses on identifying and addressing various physical, psychosocial and spiritual needs of patients with life-threatening illnesses, should not only be provided at a stadium close to death, but concurrently with oncological treatment [2].

Multiple studies, including several randomized controlled trials, have shown the benefits of early implementation of palliative care concurrently to standard cancer care for patients and their caregivers. It is for example associated with improved symptom control, quality of life and mood, satisfaction with care, coping, understanding of disease and communication about care [3–9]. It can also lead to a decrease in chemotherapy use near end of life and therefore reduce treatment costs [7, 10]. Besides, it has been shown that patients suffering from advanced cancer prefer an early talk about end-of-life topics [11–14].

Addressing palliative care and end-of-life topics should be initiated by the primary care provider of the cancer patient [15, 16]. Since not every patient is cared for by an oncologist, but by other specialists such as gynaecologists, urologists, etc. [17], all physicians treating patients with advanced cancer should aim for early implementation of palliative care into standard oncology care.

Early integration is also recommended by national and international guidelines [2, 15, 18, 19]. The basis and central component of it is communication [20], which at the same time impedes it. Previous findings show that if conversation about palliative care and end-of-life topics occur, then usually too late, when patients are no longer able to decide for their own or already are in crisis [21]. This indicates that physicians seem to avoid referring to palliative care services, which has been confirmed in previous research [22, 23]. Studies and reviews report several reasons and possible barriers to referring to palliative care services. An important barrier is a lack of physicians’ expert knowledge in palliative care, including a wrong understanding of this discipline [24]. A majority of physicians falsely equates palliative care with end-of-life care and associates it with imminent death [16], which often results in the fear of demoralizing the patient when addressing palliative care [23]. Another key reason represents the perceived difficulty to address end-of-life topics [11]. It is reported to be one of the most stressful and difficult parts within oncological treatment [25]. That discomfort is especially based on a high communicative uncertainty [11, 24]. Besides the concern of causing stress in the patients [24], also personal reasons like prior traumatic experiences [22] may lead to a lack of discussing palliative care. Thus, also the physicians’ own attitudes and fears towards death seem to play a role when avoiding such consultations [26, 27].

These aspects illustrate that physicians would benefit from offers to facilitate addressing palliative care in medical consultations with cancer patients. This is confirmed by the fact that physicians themselves demand for more education on communication in palliative care [28]. Strengthening physicians’ communication skills and reducing individual insecurities would as a result promote the timely involvement of palliative care into standard cancer care, as it is required by clinical guidelines [2, 15, 18, 19].

Various studies provide evidence for the effectiveness of communication skills trainings in oncological settings [29–32]. Also, trainings focusing on communication with regard to specific facets of palliative care, such as the transition to palliative care, have shown to be useful [30, 33]. Those trainings in most cases refer to rehearsing one specific conversation, in which the respective topic is communicated [30, 33, 34].

Until now there are no training programs which address the general ability of physicians to talk about different topics relevant to palliative care, to allow for a gradual integration of this field. Also, most existing training programs are designed for oncologists and not open to physicians of different specialisation. Moreover, previous trainings are often very intensive and time-consuming, sometimes lasting multiple days [35].

The objective of this study is to carry out an evaluation of a newly developed communication skills training within a randomized controlled trial. The training aims at strengthening the physicians’ ability to address palliative care related topics adequately and early during disease trajectory.

The main research question is:
Does the training improve communication skills and consulting competencies addressing palliative care related topics?

Further research questions concerning the effectiveness and acceptance of the training are:
Does the training improve the quality of physician-patient interaction in conversations about palliative care?Does the training support physicians to consider palliative care principles, such as psychosocial needs, within the consultation?Does the training improve the perceived confidence of physicians dealing with palliative care related topics?Does the training enhance self-efficacy regarding conversations about palliative care?Does the training change the physicians’ attitude towards caring for terminally ill patients and communicating about dying and death?Does the training improve basic knowledge about palliative care services?What is the level of acceptance and satisfaction with the training?

## Methods

### Design

The planned evaluation is designed as a prospective, multi-centered, two-armed randomized controlled trial (RCT).

The aim of the study is to investigate the effect of an intervention with regard to communication about palliative care. It will be carried out at four locations in Germany. Physicians of different specialist qualifications will be recruited and randomly assigned to an intervention group (IG) receiving the communication skills training and a wait list control group (CG). Data of both groups will be assessed 6 to 10 weeks before (baseline, T0) and 6 to 10 weeks after the training (T1). The CG will be assessed at parallel time-points and will attend the training after the end of data collection.

### Cooperation partners

The study will be carried out at four sites with partners with long-term experience in palliative care. Study sites are located at the University Medical Center Hamburg-Eppendorf, the University Medical Center Goettingen, the University Medical Center Schleswig-Holstein and the Charite University Medicine Berlin. Trainings and data collection will be carried out at all four locations. Coordination, training development and data analysis will mainly be conducted in Hamburg, where the principal investigator and the study management are situated.

### Inclusion and exclusion criteria

Eligible for the RCT are physicians who treat cancer patients in their daily routine but are not specialized in palliative care. Participation is not limited to medical oncologists, but open to all physicians treating cancer patients (such as gynecologists, dermatologists, urologists etc.). Participants must provide informed consent for participation in the study. Exclusion criteria are a palliative care specialist training level as well as insufficient German language skills, since the training is conducted in German.

### Development of the intervention

The communication skills training was developed based on literature and four focus groups (with *N* = 28 participants). Within the focus groups the perceptions and needs of physicians treating advanced cancer patients were assessed. Results were merged with relevant aspects from literature, such as the *core competencies in palliative care* defined by the *European Association for Palliative Care* (EAPC) [36]. The training was manualized following the *CReDECI2-Guidelines* (Criteria for Reporting the Development and Evaluation of Complex Intervention in healthcare: revised guideline) [37].

The newly developed communication skills training consists of two sessions each lasting 90 min. It includes short theoretical presentations, written information, audiovisual contents as well as behavioral exercises for active learning. Video material of an expert leading a conversation with a standardized simulated patient (SP) will be presented as a positive example within the training. The intervention is intended to promote the three components of the ‘KSA-Framework’ (Knowledge, Skills, Attitude) [38]. The component ‘knowledge’ includes theory on communication (e.g. specific skills, empathy, dealing with palliative care and end-of-life issues), core principles and concepts of palliative care (e.g. double awareness) and palliative care services. ‘Skills’ will be promoted through rehearsing conversations in role plays with SPs based on case vignettes of advanced cancer patients, which is an effective training strategies for communication skills trainings [39]. ‘Attitude’ will be addressed through the transmission of a new attitude towards palliative care and dealing with advanced cancer patients.

#### Train-the-trainer workshop

As recommended in guidelines on communication skills trainings [32], the study partners who will conduct the training will attend a train-the-trainer workshop, which will be carried out by the coordinating center. The main content will be the correct implementation of the training manual. Moreover, participants will be taught how to train future study staff as well as instructing SPs for the consultations pre and post training in the IG and CG. When SPs will be briefed in the respective study sites, a member from the principal investigator’s team will be present to ensure standardization.

### Evaluation of the training (RCT)

The communication skills training will be implemented and evaluated. The procedure of the RCT is presented in Fig. 1. The IG will receive the training between the two measurement points, while the control group receives it after the end of data collection.

**Fig. 1 Fig1:**
[figure not shown]
Flowchart of the randomized controlled trial (RCT)

#### Sample size and power

Sample size calculation indicates that a total sample size of 134 participating physicians (67 per group) is needed to detect medium group differences (Cohen’s *d* = 0.5) in a two tailed test with a power of 0.80 (80%) at a significance level of *p* < 0.05. A medium correlation (*r* = 0.3 [40]) between initial level and outcome measurement is assumed. Based on an estimated dropout-rate of 30%, recruitment of 174 physicians (87 per group) is necessary.

This amount of participating physicians will be recruited consecutively in groups of 10 and equally divided between the four study sites. For the recruitment, information material will be spread in local oncological networks, at conferences and events.

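### The 30% dropout allowance multiplies 134 by 1.3 instead of dividing by 0.7, so 174 recruits leave about 122 completers, not the 134 required

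*Protocol article*

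**What the plan says.** All the figures stand in one paragraph of the protocol article, under Methods, Sample size and power. It first fixes the number of physicians the comparison requires: a "total sample size of 134 participating physicians (67 per group) is needed to detect medium group differences", with Cohen's d = 0.5, a two-tailed test, 80% power and a 0.05 significance level. A correlation of 0.3 "between initial level and outcome measurement is assumed". It then allows for losses: "Based on an estimated dropout-rate of 30%, recruitment of 174 physicians (87 per group) is necessary".

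No other section gives a different dropout rate, number of completers or recruitment target. The Randomization section gives 1:1 allocation. The Data analyses section names linear mixed models adjusted for the T0 level of the outcome as the analysis of the training effect.

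**The concern.** The paragraph links three numbers: 134 needed, 30% lost, 174 recruited. The third is meant to follow from the first two, so that taking 30% off the recruits leaves the number needed. It does not. The ratio 174/134 is 1.30, which suggests that 30% of the completers was added, instead of finding the number that leaves 134 after 30% of it is lost.

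The recruitment target is the figure by which completion of enrolment is judged. If it is too low for the stated dropout, a trial that goes exactly to plan still ends below its own stated requirement, and the power statement attached to 134 does not describe the data expected at analysis.

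**Working it through.** **Inputs** (all from Sample size and power, except allocation, from Randomization): N needed = 134 (67 per group); dropout q = 0.30; N recruited = 174 (87 per group); d = 0.5; two-sided α = 0.05; target power 80%; r = 0.3; 1:1 allocation.

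**1. Reproducing the stated target.** N × (1 + q):
- total: 134 × 1.30 = 174.2
- per group: 67 × 1.30 = 87.1

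Rounded down, these are the stated 174 and 87.

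**2. The inflation that preserves 134 completers.** N / (1 − q):
- total: 134 / 0.70 = 191.4, so 192
- per group: 67 / 0.70 = 95.7, so 96

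This is 192 − 174 = 18 more than stated, too large a gap for rounding.

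**3. Forward check of the stated target.** N recruited × (1 − q):
- total: 174 × 0.70 = 121.8, about 122
- per group: 87 × 0.70 = 60.9, about 61
- shortfall: 134 − 122 = 12

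**4. Dropout that 174 can bear.** 1 − 134/174 = 40/174 = 23.0%.

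**5. Power for the completers.** Noncentral t with n per group and noncentrality (d/√v) × √(n/2). For an unadjusted t-test v = 1 and df = 2n − 2. For baseline adjustment v = 1 − r² = 0.91 and df = 2n − 3.

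| n per group | Unadjusted t-test | Baseline-adjusted, r = 0.3 |
|---|---|---|
| 61 | 78.2% | 81.9% |
| 67 | 81.9% | 85.3% |

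Noncentralities at n = 61: 0.5 × √30.5 = 2.761 unadjusted; 2.761/√0.91 = 2.895 adjusted. At n = 67: 2.894 and 3.034.

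**6. Where 134 itself comes from.** With d = 0.5 and 80% power, the smallest n per group is:
- unadjusted t-test: 64 (total 128)
- baseline-adjusted with r = 0.3: 59 (total 118)
- change score, variance factor 2(1 − r) = 1.4: 89 (total 178)
- Wilcoxon–Mann–Whitney with relative efficiency 3/π: 67 (total 134, power 80.1%)

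Of these, only the Wilcoxon variant returns 134, and it does not use r. Under that variant 61 per group give 76.3%. The protocol does not name the test behind 134, so this match is an inference. Steps 1 to 4 do not depend on it.

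**The case against.** The arithmetic is not in dispute; the argument is about how much it matters. The planned analysis adjusts for the T0 level, and the protocol assumes r = 0.3. On those inputs 118 completers suffice for 80% power, and 118 / 0.70 = 168.6, so 169 recruits would be enough, fewer than 174. The 61 per group left after 30% dropout give 81.9%, still above target. The 78.2% figure belongs to an unadjusted test, which the Data analyses section does not use for the training effect. On this view the trial falls short only of a headcount that its own inputs do not reproduce under its own model.

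This stands as a statement about size. Under the planned model with independent observations, the 80% target is still met. It does not repair the paragraph, which names 134 as the number needed and derives 174 from it.

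Two possible rescues fail:
- **Reading 30% as a mark-up on completers.** This returns 174, but it is not what a dropout rate ordinarily means. It corresponds to 23% of those recruited, which the text does not say.
- **The mixed model's handling of missing data.** There is one post-training measurement and the T0 value is the covariate, so a physician without T1 adds little or nothing to the group contrast.

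The margin above 80% is also thin. Training is given in groups of up to 10, and the stated calculation mentions no clustering. The document gives no intraclass correlation. As an assumption, take clustering in the trained arm only, with 7 completers per training group, so that the arm's variance is multiplied by 1 + 6 × ICC. Baseline-adjusted power at 61 per group is then about 81%, 80% and 76% for ICC 0.01, 0.02 and 0.05, against about 84%, 83% and 80% at 67 per group. Clustering is a separate question and would affect 134 completers too, but it shows what the 12 lost completers could have absorbed.

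**Conclusion.** The concern holds. At the stated 30% dropout, 174 recruits do not deliver 134 completers: they deliver about 122, a shortfall of 12 (6 per group). The correct inflation of 134 is 192, and 174 is consistent with 134 only if dropout does not exceed 23.0%. This rests on nothing beyond the paragraph's own figures and the ordinary meaning of a dropout rate.

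The cost in power is about 3 to 4 percentage points: from 85.3% to 81.9% with baseline adjustment at r = 0.3, or from 81.9% to 78.2% without it. These values assume d = 0.5, equal losses in both groups and independent physicians. The planned analysis therefore stays just above 80% before any clustering. The error needs correcting because the stated recruitment target is wrong as derived, not because power collapses.

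**What to change.** Correct the sentence on dropout in Sample size and power. Either of these is sufficient, and neither needs more recruits:

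- Keep 174 and 30%. State that about 122 completers (61 per group) are expected, and give the power for that number under the primary analysis, naming the test and how r enters. With baseline adjustment at r = 0.3 and no clustering this is 81.9%.
- Keep 174 and 134. State that the target of 134 is met only if dropout is at most 23%.

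In both cases give 192 (96 per group) as the correct inflation of 134 at 30% dropout, and make clear that it answers the headcount of 134. It is not the number required for 80% power under the baseline-adjusted model.

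The cost is one sentence, with a stated power or tolerable dropout slightly less favourable than the present text implies. Randomization, design and analysis do not change.

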#### Randomization

Computer generated randomization for all study sites will be performed by an experienced independent co-worker from the statistical-methods-group of the Department of Medical Psychology at the University Medical Center Hamburg-Eppendorf. Randomization will be conducted separately per site. Since participants will be recruited consecutively, block randomization with block sizes of 20 will be applied. Within every block of 20 participants at each study site, 10 will be assigned to IG and 10 to CG. Allocation ratio of 1:1 will be used.

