#### Primary outcome

##### Communication skills and consulting competencies addressing palliative care related topics

In order to assess the consultation performance of the physicians, we will develop different case vignettes, which will be varied systematically between the measurement points. While the severity of the disease will be comparable, the type of symptoms and the patient’s needs will differ from case to case.

Communication skills and consulting competencies addressing palliative care related topics will be assessed by the research team using the German version of the COM-ON-checklist (COM-ON = *Communication in Oncology*) [41], which is a valid instrument for the external assessment of communication behavior of oncologists consisting of 5 scales and 31 Items. Researchers will rate the videotaped physician-patient-consultations on a 5-point Likert scale by the following scales: *general communication skills*, *specific skills: transition to palliative care*, *involvement of relatives* and *overall evaluation items*. The fifth scale named *disclosing information about clinical trials* will be excluded, because in this context no such information has to be given, so that only 21 items are used. The instrument has proved to be valid and reliable [41].

To ensure independent and blinded rating of the consultation, we will rotate the videotapes between the four research sites. Thus, the rater will not have any information on group membership (IG or CG) of the respective participant.

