### Data analyses

This study is a multivariate, two-armed RCT with repeated measurement points across time. Descriptive statistics will be used to characterize and describe groups (IG and CG). Using univariate analyses (t-test, analysis of variance) or comparable non-parametric tests (chi-square-tests, U-tests), differences between subgroups (e.g. age, medical specialization, level of working experience, work setting) will be explored.

In order to measure the success of the training, covariate-adjusted linear mixed models will be conducted for analyzing primary and secondary outcome variables. The considered covariates will be the initial level of outcome variables at T0. This method allows to also consider missing data. For non-repeated continuous and binary measurements, ordinary linear regression and logistic models will be used.

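### Site stratifies the randomisation but is not named in the outcome models: a small, avoidable loss of efficiency

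*Protocol article*

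**What the plan says.** Under Randomization, the protocol article makes site a stratification factor: "Randomization will be conducted separately per site". It adds "Within every block of 20 participants at each study site, 10 will be assigned to IG and 10 to CG", so the arms are balanced inside each of the four sites, apart from incomplete blocks and dropout.

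Under Data analyses, it states that "covariate-adjusted linear mixed models will be conducted for analyzing primary and secondary outcome variables" and then names the adjustment set: "The considered covariates will be the initial level of outcome variables at T0". Site is not mentioned in that section, either as a fixed or as a random effect. What the random part of the mixed model contains is not stated.

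**The concern.** An analysis should normally reflect the restrictions used in the randomisation. Balancing the arms within sites removes site differences from the actual sampling error of the treatment contrast. A model without site does not know this: it counts the site differences as residual noise. The reported standard error then exceeds the true one, confidence intervals are too wide, and the test rejects less often than its nominal 5% under the null.

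The article gives some reason to expect site differences common to both arms. Recruitment uses local networks (Sample size and power), and simulated patients are briefed at the individual sites (Train-the-trainer workshop). Adjusting for T0 removes only part of a stable site difference, since the assumed correlation between T0 and outcome is 0.3.

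At stake is some power and the calibration of the test. The validity of the estimate is not in question.

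**Working it through.** **Inputs from the article.** From Sample size and power: d = 0.5 (SD 1), two-sided alpha 0.05, target power 0.80, r = 0.3, 67 analysed per arm, 87 recruited per arm, 30% dropout, equal split over four sites. From Randomization: 1:1 within site.

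**Assumption.** The share ρ of the T0-adjusted residual variance that lies between sites is not given. I use 0, 5, 10 and 20%. Because ρ is defined after T0 adjustment, whatever T0 already removes is excluded from it.

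**The plan's own figure.** With T0 adjustment the residual variance is 1 − 0.3² = 0.91. For 80% power this needs 58 (normal) or 59 (t) per arm; with no covariate, 63 or 64. The stated 67 is not reproduced and exceeds what its inputs require. That is a separate matter. It is relevant here only because it leaves a reserve of power. The stated dropout applied to the stated recruitment gives 87 × 0.7 = 60.9 per arm, so I show both 60 (15 per arm at each site) and 67.

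**Formulas, n per arm.**
- True SE (arms balanced within site): √(0.91(1 − ρ)) × √(2/n).
- SE reported without site: √0.91 × √(2/n), so reported/true = 1/√(1 − ρ).
- Type I error without site: two-sided t tail beyond t(0.975, 2n − 3)/√(1 − ρ).
- Power without site: noncentral t beyond that same threshold, noncentrality 0.5/true SE.
- Power with site: noncentral t with the true SE and 2n − 6 degrees of freedom.

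**One case in full (ρ = 0.10, n = 67).** True SE = √0.819 × √(2/67) = 0.1564. Reported SE = √0.91 × √(2/67) = 0.1648. Ratio 1.054. The critical value 1.978 acts as 1.978 × 1.054 = 2.085, giving a type I error of 3.9%. With site, noncentrality is 0.5/0.1564 = 3.20 on 128 degrees of freedom, giving power of 88.8%, against 86.6% without site.

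| Site share ρ | Reported/true SE | Type I error without site | Power at 60 per arm, without → with site | Power at 67 per arm, without → with site |
|---|---|---|---|---|
| 0% | 1.000 | 5.0% | 81.3 → 81.2% | 85.3 → 85.3% |
| 5% | 1.026 | 4.4% | 81.9 → 83.2% | 86.0 → 87.1% |
| 10% | 1.054 | 3.9% | 82.5 → 85.1% | 86.6 → 88.8% |
| 20% | 1.118 | 2.9% | 83.9 → 88.9% | 88.0 → 92.0% |

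**Simulation check** (20,000 trials per case, 4 sites × 34, T0 in both models). Type I error without site was 4.9, 4.2, 3.9 and 2.7%; with site, 4.9, 4.8, 5.0 and 4.9%. Power rose by 0.1, 1.1, 2.2 and 4.1 points. Both agree with the table.

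**The case against.** The strongest reply is that the model is not fully described. It is a mixed model with an unstated random part, the article is condensed, and the analysis plan is not shown, so a site random effect may be intended. That stands as a limit: the article does not exclude site. It does not remove the point, because the covariates are listed and the stratification factor is not among them. Someone implementing the section as written would leave site out.

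It is also fair that the loss is small and rests on an assumed variance. The article describes steps that limit site differences: a train-the-trainer workshop, a manual, and a member of the coordinating team present when simulated patients are briefed. A site share near zero is possible, and then nothing is lost.

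Some stronger readings are tempting but not supported:
- A reader might infer that omitting site leaves the trial underpowered. With T0 in the model and the article's own d and r, power stays above 80% in every case computed. Figures below 80% at about 60 per arm arise only if the T0 adjustment is ignored.
- A reader might infer bias or false-positive inflation. Balance within site protects the estimate, and the test errs on the conservative side.
- A reader might count the local trainers as a source of site variation common to both arms. The control group is untrained until data collection ends, so trainer differences act only in the intervention arm; a site main effect does not model them.
- A reader might want a rating-site term because "we will rotate the videotapes between the four research sites". The rotation scheme is not described, so the article does not establish the need for one.

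**Conclusion.** The point holds as a minor matter of efficiency and calibration. Site stratifies the allocation and is missing from the stated adjustment set. Run as written, the primary and secondary models would report a standard error too large by 0 to about 12% over site shares of 0 to 20%, and would give up 0 to about 5 power points. At shares up to 10% the loss is no more than about 3 points.

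The direction is certain if site is left out and its variance is not zero. The size is not, because it depends on a site variance that the documents do not give. The figures also assume balance within sites, a constant treatment effect across sites, and the article's d = 0.5 and r = 0.3.

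**What to change.** In Data analyses, add study site (4 levels) as a fixed effect alongside the T0 value in the models for the primary and secondary outcomes that compare IG with CG. Acceptance of and satisfaction with the training involves no such comparison before the control group is trained, and needs no change.

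A stated random site effect would also be defensible; with only four sites a fixed effect is simpler and does not require estimating a variance from four levels. Whichever is used, naming it in advance removes a later choice between models with and without site.

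The cost is one sentence and 3 degrees of freedom. No new data are needed, since site is known at randomisation. If site turns out not to matter, power changes by about 0.1 point or less.
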